## Abstract

**Background:**

Scaphoid fractures are the most common carpal fractures. They often need to be treated by surgery, where the use of a compression screw is the globally accepted gold standard. Surgeons may choose between different implant materials including titanium alloys, which remain in the body or are removed after healing. An alternative are biodegradable magnesium-based implants. Properties of magnesium alloys include high stability, osteoconductivity, potential reduction of infections and few artifacts in magnetic resonance imaging (MRI). The aim of this trial is to demonstrate non-inferiority of magnesium-based compression screws compared with titanium Herbert screws for scaphoid fractures.

**Methods:**

The trial is designed as a multicenter, blinded observer, randomized controlled parallel two-group post market trial. Approximately 190 patients will be randomized (1:1) with stratification by center either to titanium or magnesium-based compression screws. Follow-up is 1 year per patient. Surgical procedures and aftercare will be performed according to the German treatment guideline for scaphoid fractures. The first primary endpoint is the patient-rated wrist evaluation (PRWE) score after 6 months. The second primary endpoint is a composite safety endpoint including bone union until 6 months, no adverse device effect (ADE) during surgery or wound healing and no serious ADE or reoperation within 1 year. The third primary endpoint is the difference in change MRI artifacts over time. Non-inferiority will be investigated for primary endpoints 1 (t-test confidence interval) and 2 (Wilson’s score interval) using both the full analysis set (FAS) and the per protocol population at the one-sided 2.5% test-level. Superiority of magnesium over titanium screws will be established using the FAS at the two-sided 5% test-level (Welch test) only if non-inferiority has been established for both primary endpoints. Secondary endpoints include quality of life.

**Discussion:**

This study will inform care providers whether biodegradable magnesium-based implants are non-inferior to standard titanium Herbert screws for the treatment of scaphoid fractures in terms of wrist function and safety. Furthermore, superiority of magnesium-based implants may be demonstrated using MRI, which is used as surrogate endpoint for screw degradation.

**Trial registration:**

DRKS, DRKS00013368. Registered Dec 04, 2017.

**Electronic supplementary material:**

The online version of this article (10.1186/s12891-019-2723-9) contains supplementary material, which is available to authorized users.

## Background

The fracture of the scaphoid is the most common carpal fracture accounting for 2 to 7% of all fractures [1], and young men between 20 and 29 years are predominantly affected [2]. This has an economic impact on the society caused by the absence from work. Therefore, the goals of treatment are to avoid long immobilization, bone healing disorders i.e., pseudarthrosis of the scaphoid and to gain normal wrist function.

The probability for bone healing mainly depends on displacement and location of the fracture and decreases substantially if the fracture gap width exceeds 2 mm [3]. Surgical treatment is generally recommended for unstable fractures, which include fractures with displacement ≥1 mm or ≥ 2 mm, comminuted fractures, perilunate fracture-dislocation and all fractures in the proximal third because of a long immobilization time and a high risk for pseudarthrosis [4]. Conservative treatment is often recommended for stable fractures [5]. Specifically, the German treatment guideline for scaphoid fractures [6] recommends conservative treatment of tubercle fractures (type A1) and non-dislocated transverse fractures in the middle or distal third (type A2) for the classification scheme by Herbert and modified by Krimmer et al. [4]. Recommendations for operative treatment have, however, been expanded in recent years to include non-displaced waist fractures to avoid long periods of immobilization and by that resulting joint stiffness [5], and the German treatment guideline recommends minimal invasive surgery for A2 fractures.

Headless compression screws are considered to be particularly well suited for surgical therapy of recent fractures [6], which can be inserted through both palmar and dorsal approaches. Most frequently, non-biodegradable metallic implants are used, specifically titanium or steel alloys. However, surgeons may also choose absorbable implants, e.g., polymer-based implants [7] and magnesium-based implants [8, 9], which have the clear advantage that they degrade over time so that no second surgery is required for implant removal [10, 11]. Screw removal rates between 8 and 14% have been reported for various indications in the literature [12–14]. A major advantage of magnesium-based implants over polymer implants is their higher stability [8, 9]. They also have osteoconductive properties [9] and are supposed to inhibit infections [9].

### Few artifacts in magnetic resonance imaging and computed tomography scans

Furthermore, magnesium-based implants produce almost no artifacts in MRI or CT even when imaging was done immediately after implantation [9, 15]. In contrast, titanium screws generally create interference. On the 3 T scanner employed by Sonnow et al. [15], the largest difference in artifacts between magnesium-based and titanium implants was observed when imaging was done with the T1w turbo spin echo (TSE) sequences. Fewer artifacts were also observed for the proton density weighted (PDw) TSE and PDw TSE metal-artifact reduction (WARP) sequences. However, differences were less pronounced.

Magnesium-based implants thus better facilitate post-operative follow-up. In addition, since magnesium-based implants are biodegradable, a further reduction of artifacts over time is expected. Change of artifact size over time may thus serve as surrogate marker for screw degradation.

### Magnesium-based compression screw

MAGNEZIX® CS of Syntellix AG are magnesium-based Herbert screws. The alloy is based on the MgYREZr/WE43 system and contains more than 90% magnesium and, in addition, yttrium, rare earth metal and zirconium. It is free of aluminium, a well-known neurotoxin [16]. MAGNEZIX® CS has market approval for the European Union, countries belonging to the European Free Trade Association and 21 additional countries worldwide (as of July 31, 2018). The small CS 2.0 is not cannulated, while CS 2.7 and CS 3.2 are cannulated to allow insertion of a guide wire (Fig. 1). All screw models have a self-cutting tip to ease insertion. During screw implantation, specially modified instruments are used.

**Fig. 1 Fig1:**

Magnesium-based compression screws to be used in this trial. From left to right: MAGNEZIX® CS 2.0, MAGNEZIX® CS 2.7, MAGNEZIX® CS 3.2

### Radiolucent zone around any part of the implant

Radiolucent zones around magnesium-based implants have been described in the literature [17, 18]. Although this may be visually inconvenient, this effect is only short-term, it does not affect bone healing and disappears automatically over time. Experiences from laboratory testing animal studies have shown the disappearance of the screw within 1 year [17, 18], and in a clinical trial it was degraded after 3 years [19].

In summary, radiolucent zones are expected during the degradation of the screw because of the material properties of magnesium and its degradation via corrosion. Consequently, this effect is not taken account as a screw-related complication.

### Breakage of magnesium-based screws in the healing process

When the healing process is well advanced, MAGNEZIX® implants will be recognized as being deformed in diagnostic imaging caused by the degeneration process of the implant. In this process, these implants did not break because of a lack of stability, but they were degrading as intended, while the bone continued to heal and gradually bore higher load capacity.

In summary, the breakage of MAGNEZIX® CS during the healing process may occur due to the degradation process. Consequently, this effect is not considered a screw-related complication.

### Clinical evidence of magnesium-based screws

In an RCT, biodegradable magnesium-based screws were not inferior to titanium screws for the treatment of mild hallux valgus deformities [20]. Primary endpoint of this trial was the absolute difference between the distal metatarsal articular angle (DMAA) measured 6 months post-surgery and immediately post-surgery. The authors also measured the American Orthopedic Foot and Ankle Society (AOFAS) score for hallux, visual analog scale (VAS) for pain assessment and range of motion (ROM) of the first metatarsophalangeal (MTP-IP) joint. The authors observed comparable values between titanium and magnesium-based screws for these outcome variables. In addition, no foreign body reactions, osteolysis and systemic inflammatory reactions were detected. During the implants’ absorption process, no increase of the laboratory values of electrolytes including magnesium or other components or degradation products of the magnesium-based screw were found [20]. Three-year follow-up data to this trial have been reported [19].

Magnesium-based compression screws are meanwhile used in several indications, e.g., for the treatment of hallux valgus [19–22], malleolar fractures [23, 24], ankle joint fractures [25], in the treatment of fibula fractures [25], scaphoid fractures [26, 27] or radial head fractures [28].

### The need for a trial

Windhagen et al. [20] focused on elective foot surgery. However, an RCT for the use of magnesium-based screws is lacking in fractures, especially in scaphoid fractures. This trial is required to show the non-inferiority of magnesium-based screws compared to conventional titanium screws in hand and trauma surgery.

### Study objectives and hypotheses

The general aim of this trial is to obtain precise, well-founded and systematic application data of biodegradable magnesium-based compression screws compared to conventional titanium compression screws for the treatment of scaphoid fractures.

Specifically, we hypothesized that biodegradable magnesium-based compression screws are non-inferior compared with titanium screws in the treatment of isolated scaphoid fractures in terms of both efficacy and safety. In addition, we hypothesize that magnesium-based compression screws are superior to titanium screws in image analysis because magnesium-based compression screws are biodegradable.

The primary objective of this trial thus is to determine non-inferiority for efficacy and safety of magnesium-based compression screws when compared to titanium screws in the surgical treatment of patients with scaphoid fracture. If non-inferiority can be shown for both efficacy and safety, the final primary aim is to demonstrate superiority of magnesium-based compression screws over titanium screws with the surrogate variable artifact reduction as indicator for degradation of magnesium-based compression screws in-vivo.

Secondary objective of the trial is to compare quality of life in patients treated with magnesium-based compression screws with classical Herbert titanium screws.

## Methods

### Study design

SCAMAG is a randomized, controlled, parallel-group, open-label with blinded observer, multicenter trial with two groups for comparing biodegradable magnesium-based screws with standard titanium Herbert screws. The study protocol follows the SPIRIT statement [29]. Reporting will follow the CONSORT statement [30] and its extension to abstracts [31].

Following the SPIRIT statement, we have created Additional file 1 to show the proposed participant flow through the study. The SPIRIT checklist is shown in Additional file 2.

The study was approved by the ethics committee of the Hanover Medical School (MHH) on September 27, 2017 (registration number: 7614), and it was registered with the German Register for Clinical Trials (DRKS, drks.de) on Dec 04, 2017 (registration number: DRKS00013368).

### Setting, recruitment, inclusion and exclusion criteria

After diagnosis of a scaphoid fracture and when a decision for the indication of an osteosynthesis with compression screw is made, patients will be recruited by the surgeon in 13 high-volume centers in Germany. Each center has experience in conducting clinical trials, treating patients with scaphoid fractures and the use of both MAGNEZIX® CS compression screws and titanium Herbert screws. All surgeons are trained in fixation of scaphoid fractures with titanium Herbert screws and MAGNEZIX® CS compression screws prior to the trial.

Study centers will receive a case payment of 500 € in two parts. The first payment in the amount of 50% will be paid after surgery and the second part after 12 months, if complete follow-up data is available.

Inclusion and exclusion criteria are displayed in Table 1.

**Table 1 Tab1:** Inclusion and exclusion criteria

Inclusion criteria: • Indication for screw fixation of scaphoid fracture which is not older than 12 weeks; classification by Herbert, modified by Krimmer of types A2, B1, B2, B3 [4], • normal wrist function prior to fracture, • age ≥ 18 years, • written informed consent for trial participation and surgery. Exclusion criteria: • Previous surgery on the wrist, associated injuries, state after or suspicion of complex regional pain syndrome (CRPS), • simultaneous fractures of the forearm of both sides and those who will influence the postoperative care, • known ligamentary concomitant injuries of the wrist on both sides and those who will influence the post-operative care, • radiological findings of medium to high grade osteoporosis, • intended or conducted spongiosa transplantation or bone graft transplantation during surgery, • pregnancy, suspected pregnancy or breastfeeding period, • allergies to components of osteosynthesis material, • participation in other clinical trials up to 30 days before inclusion in this trial, • central neurological deficits which do not permit a compliance to the trial, especially during follow-up, • for patients recruited to the centers near Hanover and undergoing MRI: claustrophobia and metallic implants which are contraindicative for an MRI.	

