### Randomization

Patients will be randomized individually to one of the two treatment groups in a 1:1 ratio in the order they qualify. After inclusion and exclusion criteria have been checked, the presence of the informed consent form has been ticked and the form has been electronically signed by the surgeon, the randomization result will be displayed in the trial database after anesthesia. Permuted block randomization is used with variable block length stratified by center. Randomization lists for the PBR will be generated using the randomization software RITA [43]. Concealment of allocation will be guaranteed through central randomization within the electronic case report form (eCRF) according to Standard Operating Procedures (SOP).

An expert reviewer pointed out that the trial might have benefited from stratification by fracture type. The decision was to stratify by center because strata would have become very small in case of stratification by center and fracture type. Preference was given to center because of its known effect and its mentioning in the International Conference on Harmonisation (ICH) E9 guideline [44].

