### Statistical analysis

All statistical analyses will be described in detail in a statistical analysis plan (SAP) which will be finalized before the randomization of the last patient. Analysis populations for the primary endpoints will be the full analysis set (FAS) based on the intention to treat (ITT) principle and the per protocol population (PP). Neither interim analyses nor adaptations are planned for this trial. All statistical analyses will be done using the R software.

The familywise error rate is set to 5%. The three primary hypotheses will be investigated hierarchically.

The hypothesis for the first primary endpoint is that the mean PRWE in the magnesium-based group is non-inferior to the mean PRWE in the titanium group, measured 6 months after randomization. The non-inferiority margin is 10 points; low values of the PRWE denote ‘no pain’ or ‘no difficulty’. The one-sided 97.5% confidence interval from the t-test will be estimated for judging non-inferiority. Sensitivity analyses will be performed using linear mixed models with center as random effect.

The hypothesis for the second primary endpoint is that the rate of safety events in the magnesium-based group is non-inferior to that in the titanium group within 1 year after surgery. The non-inferiority margin is 15%. The one-sided 97.5% Wilson score interval for the difference of two proportions will be estimated for judging non-inferiority [45]. Sensitivity analyses will be performed using logistic regression mixed models with center as random effect.

The type I error level is set to 2.5% one-sided for the first two primary endpoints. Non-inferiority will only be claimed ifthe hypothesis for the first primary endpoint shows non-inferiority in the FAS based on the ITT population,the hypothesis for the second primary endpoint shows non-inferiority in the FAS based on the ITT population,the hypothesis for the first primary endpoint shows non-inferiority in the PP population andthe hypothesis for the second primary endpoint shows non-inferiority in the PP population.

No adjustments will be made for multiple testing because both tests need to demonstrate non-inferiority.

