### Sample size calculations

Aim of the trial is to demonstrate non-inferiority of magnesium-based compression screws when compared with titanium Herbert screws for the fixation of scaphoid fractures. Standard deviations (SD) for the PRWE in the literature were all approximately 20 points [47]. Lange and Freitag [48] reported in their systematic review that many studies used a non-inferiority margin of 0.5 SD. This limit is used a non-inferiority margin for the planning of the scaphoid trial for the primary endpoint PRWE. This leads to the following assumptions for the sample size calculations for the first primary endpoint: Allocation ratio 1:1, type I error level 0.025 one-sided, power 0.9, expected difference between titanium and magnesium-based screws: Δ_1_ = 0, common standard deviation: σ = 20, non-inferiority margin: Δ_0_ = 10, drop-out 10%. To demonstrate non-inferiority under these assumptions, 94 patients per group, i.e., 188 patients in total are required for this trial.

If non-inferiority has been established for the first primary endpoint, the power to establish non-inferiority for the second primary endpoint, the safety endpoint is 90.64% under the following assumptions: type I error level 0.025 one-sided, event rate for magnesium-based and titanium screws: 0.9, non-inferiority margin: Δ_0_ = 0.15, drop-out 10%.

If non-inferiority has been established for the first primary endpoint and the second primary endpoint, the power to establish superiority for the third primary endpoint, the change in artifacts endpoint is virtually 100% under the following assumptions: type I error level 0.025 one-sided, expected difference between titanium and magnesium-based screws: Δ_1_ = 3.0, common standard deviation: *σ* = 1.0, sample size per group: *n*_*A*_ = *n*_*B*_ = 10, drop-out 10%, effective sample size per group: *n*_*A*_ = *n*_*B*_ = 9. The power is 56.41% if the mean difference is Δ_1_ = 1.0 instead of Δ_1_ = 3.0, and it is approximately 80% for Δ_1_ = 1.32.

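### A graft carried out during surgery is an exclusion criterion, but it can be known only after randomization and disclosure of the arm, which sits badly with an ITT-based FAS

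*Protocol article*

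**What the plan says.** All from the protocol article.

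- **Setting, recruitment, inclusion and exclusion criteria, Table 1.** One exclusion criterion is "intended or conducted spongiosa transplantation or bone graft transplantation during surgery".
- **Randomization.** The order is fixed: "After inclusion and exclusion criteria have been checked, the presence of the informed consent form has been ticked", the surgeon signs the form electronically, and then "the randomization result will be displayed in the trial database after anesthesia".
- **Baseline and follow-up examinations, Table 2.** The eligibility check and randomization are both marked in the baseline column, ahead of the surgery column.
- **Study design.** The trial is a "randomized, controlled, parallel-group, open-label with blinded observer, multicenter trial with two groups". The operating surgeon is not blinded.
- **Statistical analysis.** The analysis populations "will be the full analysis set (FAS) based on the intention to treat (ITT) principle" and the per protocol population. Non-inferiority is claimed only if it is shown in both sets for both the PRWE and the safety composite.
- No section says what happens to a randomized patient who then receives a graft.

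**The concern.** An eligibility criterion should rest on what is known before allocation. The *intended* half of this one does. The *conducted* half refers to something that happens in an operation performed by a surgeon who has been shown the arm. It can therefore turn a properly randomized patient into an ineligible one after the fact, through a decision that could depend on the screw being used.

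If a site reads the table literally and stops follow-up, the 6-month PRWE and the 1-year safety outcome are lost, and no later analysis rule brings them back. If an analyst reads it literally, the patient drops out of both the FAS and the PP set, so requiring success in both sets gives no protection. Multiple imputation does not help either, because an excluded patient is not a missing value within the analysis set. Selective removal in a non-inferiority comparison can hide a real disadvantage of the new device. It can also work the other way.

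**Working it through.** **1. The plan's own figures.** The Sample size calculations section uses "type I error level 0.025 one-sided, power 0.9", SD 20, margin 10 and 10% drop-out.

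- PRWE: n = 2(1.96 + 1.2816)² × 20²/10² = 84.06, so 85 evaluable per arm. 85 × 1.1 = 93.5, which gives the stated 94 per group (85/0.9 would give 95).
- Safety: with rate 0.9, margin 0.15 and 85 per arm, SE = √(2 × 0.9 × 0.1/85) = 0.0460. Power = Φ(0.15/0.0460 − 1.96) = 0.903, against the stated 90.64%.

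These figures reproduce closely and are not in dispute.

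**2. Order of events.** Eligibility check, signature, allocation displayed after anesthesia, screw placed, graft (if any) carried out. The last step is the only one at which *conducted* can be established, and it comes after the eligibility check and randomization.

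**3. Size of the bias in the safety difference, if grafted patients were excluded.** The article gives no graft rate and no event rate by graft status, so everything here is assumed: event risk 0.40 in grafted and 0.10 in other patients, the same in both arms; g_M and g_T are the shares grafted.

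- True difference = [0.10 + 0.30 g_M] − [0.10 + 0.30 g_T] = 0.30 (g_M − g_T).
- Difference after exclusion = 0.10 − 0.10 = 0.
- Amount hidden = 0.30 (g_M − g_T).

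| g_M vs g_T | Hidden difference | Share of 15-point margin |
|---|---|---|
| equal | 0 | 0% |
| 4% vs 2% | 0.6 points | 4% |
| 8% vs 2% | 1.8 points (12.4% − 10.6%) | 12% |
| 2% vs 4% | −0.6 points | reversed: an advantage of magnesium is hidden |

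**4. Effect on the error rate, one-sided stress case.** Take true event rates of 0.25 (magnesium) and 0.10 (titanium), exactly at the margin, with 85 per arm. Remove a share g from the magnesium arm only, with event risk q among those removed. The remaining magnesium rate is (0.25 − gq)/(1 − g). By exact enumeration of the Wilson-type interval, the type I error with nobody removed is 0.026.

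| Removed | q = 0.3 | q = 0.5 | q = 0.8 |
|---|---|---|---|
| 5% | 0.028 | 0.041 | 0.072 |
| 10% | 0.032 | 0.070 | 0.188 |

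This is a bound in one direction, not an expectation, since it allows no grafts at all among the titanium patients.

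**5. PRWE.** With SE = 20√(2/85) = 3.07, a selection shift of b points at the 10-point margin gives a one-sided error of Φ(b/3.07 − 1.96): 0.036, 0.051, 0.095 and 0.163 for b = 0.5, 1, 2 and 3. For scale, removing 5% of one arm whose mean is 20 points worse than the rest shifts that arm by 0.05 × 20 = 1 point. These inputs are also assumed.

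**6. Loss of numbers.** If the same share were excluded from both arms, the evaluable number is about 94(1 − g) × 0.9. At g = 5% that is 80 per arm, with power 0.882 (PRWE) and 0.885 (safety, normal approximation). At 15% it is 71 per arm, with 0.841 and 0.846. The loss of power is modest; the issue is selection.

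**The case against.** A reader might infer that the plan removes grafted patients from the FAS and so breaks intention to treat. The article does not support that. Table 1 governs enrolment and the Statistical analysis section governs analysis. Nothing states that a patient found to breach a criterion after randomization is withdrawn, replaced or dropped, and the stated ITT basis can be read as keeping such patients in the FAS. The detailed handling of eligibility violations normally belongs in the SAP, which is not shown, so its absence here is not a finding. All of this stands.

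A reader might also infer that grafted patients do worse and that magnesium patients would be grafted more often. Neither is documented. Surgeons are trained in both screws, procedures are otherwise the same in both arms, and planned grafts are already screened out by the *intended* half. The bias could be nil or could run against magnesium.

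Finally, the Randomization section says only that the result appears after anesthesia, not that it appears before the fracture is exposed. This weakens the timing argument only a little, because Table 2 places the eligibility check and randomization at baseline.

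What the objection does not remove is the wording itself. The criterion is stated, sites act on eligibility criteria, and half of it cannot be applied at the time eligibility is decided.

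**Conclusion.** The point holds as a badly fixed eligibility criterion. It does not hold as proof that the ITT analysis is broken. A graft conducted during surgery cannot be known when patients are declared eligible, and its use as an exclusion invites post-allocation removal by an unblinded surgeon or by an analyst. Whether that would happen is not stated.

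If it did, the bias in the safety difference would be 0.30 times the difference in graft rates under the assumed event risks of 40% and 10%. That is small against the 15-point margin for modest imbalances, zero at equal rates, and of either sign. Larger inflation of the type I error needs strongly one-sided removal of high-risk patients. The size rests entirely on assumed rates. The inconsistency in timing rests on the article's own text.

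**What to change.** 1. In Table 1, delete 'or conducted', so that the criterion covers only a graft intended before randomization.
2. State that a randomized patient who receives a graft stays in the FAS in the arm assigned, with full follow-up, and that the graft is handled as a deviation for the PP set only.
3. Report the number of grafts by arm.

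The cost is two words in the table, one sentence in the SAP and one line in the results. The FAS becomes slightly more heterogeneous. The planned sample size and power are unaffected. The change concerns eligibility and analysis sets only; no rule on when to graft is proposed.
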